## Methods/design

This pilot study is a double-blind, randomized, placebo-controlled, clinical trial assessing the effect of Exenatide compared with placebo on top of TTM in adult comatose OHCA patients. Patients are enrolled at two tertiary Danish university hospitals offering highly specialized cardiac care for a population of approximately 3,000,000 citizens.

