### Study drug administration

Preparation of study drug (Exenatide/placebo): Trained hospital nurses not taking part in the management of the patient will prepare infusion bags with Exenatide or placebo. At first notice of a potential candidate for inclusion in the trial, a set of study drug and placebo will be prepared. The infusions will be prepared as follows:

First, 1.5 ml is removed from 250 ml of isotonic NaCl and 1.5 ml of 20 % human albumin is added to prevent binding of the study drug to the infusion material. For every potentially eligible patient, two infusion kits will be prepared. One is a placebo kit as described, and one has 25 μg Byetta (Lilly, Exenatide) added. The two infusion kits are labelled ‘A’ or ‘B’ by random allocation in a computer-based randomization system and brought directly to the ICU. The random allocation will occur via the trial website with a specific logon for personnel involved in study drug preparation. The allocation ‘A’ and ‘B’ will be chosen at random by the trial website algorithm (randomization generated into dynamic blocks), stratified for site and will be unblinded by the end of trial.

The cardiologist responsible for the patient’s treatment screens the patient’s eligibility and obtains informed consent from legal representatives. If the patient is eligible for inclusion and informed consent is obtained from two independent physicians, the patient is randomized via the trial website to receive either infusion kit ‘A’ or ‘B’, and the other kit is discarded. The cardiologist orders the infusion to be given. The infusion is given in a central or peripheral intravenous line. The nurses preparing the infusion kits remain blinded to participant allocation, and the nurses initiating the study drug infusion (ICU nursing staff) remain blinded to the preparation of the infusion kits.

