Blinded efficacy variables will be recorded at 3, 30, 90 and 180 days. The telephone-based assessment will be performed by a single trained study nurse, not otherwise involved in the care of patients. Other variables will be assessed and recorded in the case report forms (CRF) by a trained physician not involved in the care of patients. The NSE and S100B plasma levels will be measured in the hospital laboratory for each site and recorded in the CRF. The study drug allocation will remain blinded until all follow-up data have been recorded. All CRFs will be entered into the trial database. The quality of data entry will be evaluated by random samples as well as range checks for data values. Individual patient data will be handled as ordinary chart records and will be kept according to national legislation.

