#### Analysis of endpoints

##### Primary outcome

The primary outcome of feasibility will be reported as the absolute percentage (with 95 % confidence interval) of patients in whom the study drug administration was initiated within 240 minutes of ROSC and the proportion in whom the study drug infusion was completed. The difference in NSE AUC between treatment groups will be tested with the independent-sample *t* test after logarithmic transformation (log2) to approximate a normal distribution. Missing NSE values will be imputed.

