##### Secondary and tertiary outcomes

Differences between treatment groups will be analysed with an independent sample *t* test or chi-Square test depending on the variable being numerical or categorical. In case of skewed data, logarithmic transformation will be applied to approximate normal distribution. Crude survival analyses stratified to the treatment groups are performed using proportional hazard models. Hazard rates will also be reported adjusted for site, sex, age, shock-able primary rhythm, and time to ROSC (logarithmically transformed). Hazard ratios will be presented with 95 % confidence intervals.

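### The primary NSE analysis is an unadjusted t test although allocation is stratified by site and NSE is assayed in each site's own laboratory; adjusting for site and the baseline variables already named would give precision at little cost

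*Protocol article*

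**What the plan says.** All of the following is in the protocol article.

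- **Allocation.** Study drug administration describes the scheme as "randomization generated into dynamic blocks), stratified for site". Methods/design gives two enrolling hospitals.
- **Assay.** Endpoints says of the two brain-injury markers: "The NSE and S100B plasma levels will be measured in the hospital laboratory for each site and recorded in the CRF". The article mentions neither a central assay nor calibration between the two laboratories.
- **Primary efficacy test.** Primary outcome fixes it: "The difference in NSE AUC between treatment groups will be tested with the independent-sample" t test after log2 transformation. No site term or covariate is named.
- **Adjustment elsewhere.** Secondary and tertiary outcomes presents hazard rates "adjusted for site, sex, age, shock-able primary rhythm, and time to ROSC (logarithmically transformed"), alongside the crude ones. Numerical secondary outcomes, which include the S100B, CK-MB and troponin T AUCs, again get a t test.
- **Level and imputation.** General principles sets a two-sided 0.025 for the primary endpoints, and 10 imputed datasets if more than 5 % of outcome data are missing.

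**The concern.** Stratified blocks make the arms nearly equal in size within each site, so a site-level difference in NSE largely cancels out of the treatment contrast. An unadjusted t test does not use this. Its pooled SD still contains the between-site variance, so the reported standard error is larger than the true sampling error. Two laboratories and two patient populations make some site difference plausible.

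The plan also treats site, sex, age, shockable rhythm and time to ROSC as worth adjusting for in the survival models, but leaves them out of the endpoint on which the trial is powered. At stake is precision in a 120-patient pilot: a wider interval for the NSE ratio and a lower chance of detecting the 20 % difference.

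**Working it through.** **Inputs from Sample size estimation and General principles:** mean AUC 50, SD 30 % of the mean (15), difference 20 % (10), 50 per group, two-sided alpha 0.025 (critical value 2.241).

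**Assumption:** the ratio r of measured NSE between the sites, because the article gives none. I take 1.0 to 1.5, with two sites of equal size.

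**1. The plan's own figure.** SE = 15 × √(2/50) = 3.0. Power = Φ(10/3.0 − 2.241) = Φ(1.092) = 86.3 %, against the stated 90 %. That mismatch is a separate matter and does not decide this point; 86.3 % is the baseline below.

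**2. Site term only, total SD held at the protocol's value.** The share of variance due to site is R² = (ln r / 2)² / SD². With balance within site, the true SE is SE_unadj × √(1 − R²), while the t test uses SE_unadj. Hence:

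- actual level of the t test = 2 × [1 − Φ(2.241 / √(1 − R²))]
- power of the t test = Φ((d − 2.241 × SE_unadj) / SE_adj)
- power of the adjusted test = Φ(d / SE_adj − 2.241)

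Worked for r = 1.3, in units of the mean: (0.1312)² / 0.30² = 0.191; SE_unadj = 0.30 × 0.2 = 0.060; SE_adj = 0.060 × √0.809 = 0.0540.

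| r (assumed) | R² | SE too wide by | Actual level of t test | Power, t test | Power, site-adjusted |
|---|---|---|---|---|---|
| 1.0 | 0 | 0 % | 0.0250 | 86.3 % | 86.3 % |
| 1.1 | 0.025 | 1.3 % | 0.0232 | 86.6 % | 87.2 % |
| 1.2 | 0.092 | 5.0 % | 0.0186 | 87.4 % | 89.6 % |
| 1.3 | 0.191 | 11 % | 0.0127 | 88.8 % | 92.9 % |
| 1.5 | 0.457 | 36 % | 0.0024 | 93.1 % | 98.9 % |

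For r of 1.1 to 1.3 the gain is 0.6 to 4.1 points. On the log scale, where the analysis is done (log-SD √ln 1.09 = 0.294, effect ln 1.25 = 0.223), it is smaller: 94.3 to 94.6 %, 95.0 to 96.1 % and 95.9 to 97.8 %, or 0.3 to 1.8 points.

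**3. Simulation check** (8,000 trials per setting, 50 per site, blocks of 4 within site, log-SD 0.294). For r = 1.0, 1.2, 1.3 and 1.5 the unadjusted test rejects under the null at 0.025, 0.018, 0.014 and 0.002. The site-adjusted test stays at 0.025 to 0.026.

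**4. A more variable biomarker.** The same section quotes 72-hour quartiles of 10 and 45. If log-normal, log-SD = ln(45/10) / (2 × 0.6745) = 1.11. With the log effect of 0.223, a site term moves power from 10.6 to 10.9 % at r = 1.3 and from 10.4 to 11.1 % at r = 1.5. Those quartiles describe one time point, so this is only a sensitivity bound for the AUC.

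**5. Baseline covariates.** These need no site difference. If they explain a share R² of the variance, the SE falls by the factor √(1 − R²). For an assumed R² of 0.20 and 0.30 the factors are 0.894 and 0.837, a fall of 11 % and 16 %. At the protocol's inputs, power goes from 86.3 % to Φ(3.333/0.894 − 2.241) = 93.1 % and Φ(3.333/0.837 − 2.241) = 95.9 %. At a log-SD of 1.11 the same reductions move it only from 10.7 % to 13.1 % and 14.8 %.

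**The case against.** A prespecified unadjusted t test is a legitimate primary analysis, especially in a pilot. It is unbiased, and any distortion is towards caution. The plan is also consistent in putting crude analyses first: the adjusted hazard rates come in addition. This stands, and it is why the point concerns efficiency only.

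Three stronger readings are tempting, and the article does not support them.

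- **The test certainly runs below 0.025 and its interval is certainly too wide.** This needs a site difference in measured NSE, and none is reported. With r = 1.0 the two analyses coincide. It also needs final allocation to be balanced within site. The stratification phrase is attached to the labelling of kits A and B; the patient-level step, "the patient is randomized via the trial website to receive either infusion kit" A or B, does not repeat it. Under simple randomization the t test keeps its level (simulated 0.023 to 0.027), although adjustment still gains power.
- **Power falls sharply.** A marked fall appears only with a very large site difference, such as 0.5 log units (65 %), added on top of the protocol's SD. The total log-SD would then be √(0.294² + 0.25²) = 0.386. The stated 30 % describes AUC overall, so site variance belongs inside it. Held there, the t test's power does not fall; it only trails the adjusted test.
- **The results would be biased or false positives more likely.** Neither follows.

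It can also be said that stratification argues for a site term alone. That is fair: the other covariates rest on precision, not on the design, and their R² is assumed. But the plan itself chose them for the hazard models, and they probably offer the larger gain.

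**Conclusion.** The point holds as an avoidable loss of precision in a method that the article states explicitly. Given a site difference and balance within site, the t test's standard error is too wide by about 1 to 11 % for between-site ratios of 1.1 to 1.3. A site term then recovers roughly 0.5 to 4 power points at the protocol's SD, towards the lower end on the log scale, and about 1 point or less if the log-SD is near 1.1. Prognostic covariates would cut the standard error by about 11–16 % if they explain 20–30 % of the variance. The direction is secure; the sizes rest on assumed site ratios and R². The treatment estimate stays unbiased and type I error is not inflated. It should be changed, but the trial does not fail without the change.

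**What to change.** Before unblinding, make the primary efficacy analysis a linear model of log2 NSE AUC on treatment, site (the stratification factor), sex, age, shockable primary rhythm and log time to ROSC. Fit it within each imputed dataset, pool the estimates, and report the back-transformed ratio with its confidence interval. Keep the unadjusted t test as a supportive analysis. Use the same model for the S100B, CK-MB and troponin T AUCs. State also whether the patient-level randomization to kit A or B is itself balanced within site.

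The cost is wording, since all the covariates are already listed under Baseline data. The downside is small but not nil: a few degrees of freedom, and any missing covariate values must be included in the imputation.

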##### Secondary and tertiary outcomes

Differences between treatment groups will be analysed with an independent sample *t* test or chi-Square test depending on the variable being numerical or categorical. In case of skewed data, logarithmic transformation will be applied to approximate normal distribution. Crude survival analyses stratified to the treatment groups are performed using proportional hazard models. Hazard rates will also be reported adjusted for site, sex, age, shock-able primary rhythm, and time to ROSC (logarithmically transformed). Hazard ratios will be presented with 95 % confidence intervals.

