## Background

While the mortality after out-of-hospital cardiac arrest (OHCA) has improved over the last decade, mortality remains as high as 90 % [1], and even after successful resuscitation and admission to an intensive care unit (ICU), the in-hospital mortality is 30–50 % [2, 3]. Anoxic brain injury remains the leading cause of death in these patients [4]. The mechanisms causing neurological damage are complex but involve both ischemia and reperfusion injury leading to tissue degeneration and loss of neurological function, the extent of which depends on duration and density of the insult [5]. Targeted temperature management (TTM) may attenuate this damage in an experimental setting [6–9], and clinical trials have shown promising results in improving neurological function and survival [10, 11]. Despite this, the optimal target temperature is debated [12], and active neuroprotection in addition to temperature management seems intuitively beneficial. Glucagon-like peptide-1 (GLP-1) analogues are approved for the treatment of type 2 diabetes but have recently been suggested to ameliorate degenerative neurological disease and reduce inflammation after ischemic cerebral stroke [13]. The GLP-1 analogue Exenatide has been shown to reduce infarct volume after focal brain ischemia in mice [14] and to reduce infarct size in a model of acute myocardial infarction (MI) and reperfusion in swine [15]. In humans, patients treated with Exenatide after MI have been shown to have a larger salvage index assessed by cardiac magnetic resonance imaging (MRI) after 3 months [16, 17]. These findings have been confirmed by later trials [18, 19]. In addition, Exenatide has been well tolerated in acutely ill patients with ST-elevation myocardial infarction with no apparent increased risk of adverse events, including hypoglycaemia or pancreatitis, compared to placebo [17].

The present trial will investigate the neuroprotective capabilities of the GLP-1 analogue Exenatide administered for 6 hours and 15 minutes within 4 hours after the return of spontaneous circulation (ROSC) in comatose patients resuscitated from OHCA.

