### Trial procedure

PHASE 1 (hospital admission to start of intervention): Unconscious patients who have been admitted to the hospital with sustained ROSC after OHCA are eligible for screening. The inclusion window is 220 minutes, i.e. from 20 minutes after ROSC (defined as ‘sustained ROSC’) until 240 minutes after ROSC. The patient’s eligibility for trial inclusion is assessed according to inclusion and exclusion criteria (Table 1). If all inclusion criteria and no exclusion criteria are met, informed consent is obtained, in accordance with Danish legislation, from two independent medical doctors not involved with the trial. Patients are then randomly allocated to active study drug or placebo via an internet-based randomization algorithm available on the trial website. Baseline characteristics are obtained.

**Table 1 Tab1:** Inclusion and exclusion criteria

Inclusion criteria
1. Age ≥ 18 years
2. OHCA of presumed cardiac cause
3. Sustained ROSC, defined as ROSC when chest compressions have not been required for 20 consecutive minutes and signs of circulation persist
4. Unconsciousness (Glasgow coma scale (GCS) < 8) after sustained ROSC
Exclusion criteria
1. Conscious patient (GCS ≥ 8)
2. Female of childbearing potential, unless a negative human chorionic gonadotropin (HCG) test can rule out pregnancy within the inclusion window
3. In-hospital cardiac arrest (IHCA)
4. OHCA of presumed non-cardiac cause, e.g. after trauma, dissection/rupture of major artery or arrest caused by hypoxia (i.e. drowning or hanging)
5. Known bleeding diathesis (medically induced coagulopathy does not exclude patient)
6. Suspected or confirmed acute intracranial bleeding
7. Suspected or confirmed acute ischemic stroke
8. Unwitnessed asystole
9. Known limitations in therapy and do-not-resuscitate order
10. Known disease making 180-day survival unlikely
11. Known pre-arrest cerebral performance category score (CPC) of 3 or 4
12. > 4 hours (240 minutes) from ROSC to randomization
13. Systolic blood pressure < 80 mmHg in spite of fluid loading/vasopressor and/or inotropic medication and/or mechanical circulatory support^a^
14. Temperature on admission < 30 °C
15. Known allergy to GLP-1 analogues, including Exenatide
16. Known pancreatitis
17. Known ketoacidosis
18. Uncorrected blood glucose at admission < 2.5 mmol/l

^a^If systolic blood pressure is recovering during the inclusion window, the patient can be included

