### Endpoints

The co-primary endpoints are as follows:Feasibility, defined as > 90 % initiation of study drug administration within 4 hours following ROSC in patients eligible for inclusionEfficacy, defined as the area under the NSE curve from admission to 72 hours post-admission. Missing data will be imputed.

Secondary endpoints are as follows:Area under the S100B curve with daily measurements until 72 hours, and absolute NSE and S100B values at 48 hours. Missing data will be imputed.Composite outcome of all-cause mortality and poor neurological function, defined as the modified Rankin Scale (mRS) 4–6 at 30 days (telephone assessment)Vital status at 7 days and at least 180 days (end of the study) after OHCA by registry-based follow-upAssessment of CPC and mRS at 90 daysArea under the creatine kinase MB (CK-MB) and troponin T curve from 0 to 24 hours. Missing data will be imputed.Safety, defined as the cumulated incidence of serious adverse events (SAE) related to the study drug: death, need for mechanical hemodynamic support, hypoglycaemia < 3.0 mmol/l, pancreatitis (S-amylase > 3 UNL), need for renal replacement therapy in the first 3 days. In addition, hypoglycaemia and pancreatitis will be reported separately as additional safety.

Tertiary endpoints are as follows:Left ventricular ejection fraction on last in-hospital echocardiography, stratified by the presence of acute myocardial infarction as the cause of cardiac arrest. Patients dying during the index administration in whom a post-TTM echocardiography is not available will be given the lowest LVEF score seen in each allocation group. Missing data will be imputed.Presence of EEG findings associated with poor prognosis and EEG performed as part of per-protocol prognosticationVital status at 180 days and telephone-based CPC and mRS at 180 daysVital status at 180 days stratified for cause of death (i.e. neurological versus cardiovascular and other – will be adjudicated by two intensive-care consultants blinded to treatment allocation)

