##### Subgroup analyses

Subgroups will be analysed according to pre-defined design variables: over or under median age, shockable rhythm, sex, the presence of shock at admission, diagnosed AMI and over or under median time from arrest to ROSC. Difference in intervention effect estimates according to subgroup will be declared exclusively based on a statistically significant test of interaction.

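### The pooled comparison of CK-MB and troponin T AUC is unadjusted and would gain precision from including ST-elevation infarction at admission

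*Protocol article*

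**What the plan says.** - **Test.** Under Secondary and tertiary outcomes: "Differences between treatment groups will be analysed with an independent sample" *t* test for numerical variables. The only refinement is "In case of skewed data, logarithmic transformation will be applied to approximate normal distribution".
- **Covariates.** Adjustment is stated for the survival models alone: "Hazard rates will also be reported adjusted for site, sex, age, shock-able primary rhythm, and time to ROSC" (the last on a log scale). Infarct status is not in that list.
- **Endpoint.** The Endpoints section lists CK-MB and troponin T AUC from 0 to 24 hours as secondary, with no stratification. The tertiary cardiac endpoint is handled differently: "Left ventricular ejection fraction on last in-hospital echocardiography, stratified by the presence of acute myocardial infarction as the cause of cardiac arrest".
- **Population and allocation.** The inclusion criterion is "OHCA of presumed cardiac cause", so infarction is not required. The allocation is "stratified for site", and no other stratification factor is named.
- **Available data.** The Baseline data section includes ST-elevation acute myocardial infarction among the admission variables.
- **Subgroups.** The predefined list includes "diagnosed AMI and over or under median time from arrest to ROSC". A difference in effect between subgroups is declared only on a significant interaction test. The endpoints covered are not named.

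**The concern.** CK-MB and troponin T are markers of myocardial injury, so their level can be expected to depend on whether the patient had an infarction. In a pooled two-sample test, that difference between patients counts as noise. It also shifts the estimate whenever the arms happen to differ in their share of infarctions, because allocation does not balance this factor.

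The plan takes infarction into account for LVEF, a tertiary endpoint, but not for the enzyme AUCs, which rank higher. The Background gives the cardiac rationale in infarction patients: "patients treated with Exenatide after MI have been shown to have a larger salvage index". The enzyme AUCs are among the few endpoints that could show such an effect, so lost precision there has a cost. The article presents these as its planned analyses and names the test, so this is a stated choice and not a detail left to another document.

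**Working it through.** **The plan's own figure.** There is none to reproduce. The only power statement concerns NSE AUC. No infarct share, enzyme level or enzyme SD appears in the documents, so the inputs below are assumptions, apart from 120 patients allocated one to one (60 per arm) and two-sided 0.05 for secondary endpoints.

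**1. Variance explained.** Let *p* be the share with ST elevation, *g* the gap in mean natural-log AUC between patients with and without it, and *w* = 1.2 the within-group log SD. Then

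R² = p(1−p)g² / [p(1−p)g² + w²], and the extra patients that adjustment is worth = 1/(1−R²) − 1 = p(1−p)g²/w².

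Gaps of 1.0, 1.5 and 2.5 are AUC ratios of about 2.7, 4.5 and 12.

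| p | g = 1.0 | g = 1.5 | g = 2.5 |
|---|---|---|---|
| 0.30 | R² 0.13, +15 % | R² 0.25, +33 % | R² 0.48, +91 % |
| 0.45 | R² 0.15, +17 % | R² 0.28, +39 % | R² 0.52, +107 % |
| 0.60 | R² 0.14, +17 % | R² 0.27, +38 % | R² 0.51, +104 % |

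Lowest cell: 0.21 × 1.0 = 0.21; 0.21/(0.21 + 1.44) = 0.13; 0.21/1.44 = 0.15. Highest cell: 0.2475 × 6.25 = 1.547; 1.547/2.987 = 0.52; 1.547/1.44 = 1.07.

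**2. Power under a second set of assumptions.** Take half the patients with infarction, w = 1.0, and a 40 % lower AUC in everyone, so δ = −ln 0.6 = 0.511. Power = Φ(δ/(SD·√(2/60)) − 1.96).

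- Adjusted, SD = 1.0: 0.511/0.1826 = 2.80, power 80 %.
- Unadjusted, fivefold AUC ratio: SD = √(1 + 0.25 × (ln 5)²) = 1.28, power 59 %.
- Unadjusted, twofold ratio: SD = 1.06, power 75 %.
- Unadjusted, tenfold ratio: SD = 1.52, power 45 %.

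Over wider ranges (p 0.3-0.6, ratio 2-10, w 0.8-1.2), the unadjusted test needs 1.07 to 3.07 times as many patients as the adjusted one.

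**3. Validity.** In 20,000 simulated trials with no drug effect (p = 0.5, ratio 5, w = 1.0), the unadjusted *t* test rejected in 5.1 %. The nominal level is kept.

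**4. Chance imbalance.** With p = 0.5 and 60 per arm, the SD of the difference in infarct share is √(2 × 0.25/60) = 0.091, so the 95 % range is about ±18 percentage points. At a fivefold ratio this moves the log difference by 0.179 × 1.609 = 0.288, a factor of up to about 1.33 in the AUC ratio.

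**5. Effect confined to infarction patients.** Take p = 0.45, g = 1.5, w = 1.2 and a 40 % reduction in patients with ST elevation only. The pooled log effect is 0.45 × ln 0.6 = −0.23.

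- Unadjusted: SD = √1.997 = 1.413, standard error 0.258, power about 14 %.
- Adjusted: standard error 1.2 × 0.1826 = 0.219, power about 18 %.

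For comparison, a 40 % reduction in everyone with the same inputs gives about 51 % unadjusted and 64 % adjusted. If the effect is confined to infarction patients, adjustment helps little, because the pooled effect itself is diluted.

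**The case against.** **The unadjusted test is legitimate.** Randomisation makes it valid, the co-primary NSE AUC is also tested without covariates, and the enzymes carry no power claim in a pilot powered on NSE. All of this stands, and it limits the point to efficiency. The baseline table will show an imbalance in ST elevation, but showing it does not correct the comparison.

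**The size is assumed.** This stands too. At a twofold ratio the loss is only 80 % to 75 % power.

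**The subgroup analysis already covers infarction.** In large part it does. Subgroup estimates by diagnosed AMI are predefined and no endpoint is excluded, so no separate request for estimates by infarct status is needed. Subgroup estimates and an interaction test still leave the main pooled comparison unadjusted.

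**ST elevation is not the variable used for LVEF.** Correct. LVEF is stratified by infarction as the cause of the arrest, which is not limited to ST elevation. Infarctions without ST elevation would stay in the other group, so ST elevation may explain less variance than infarct status would. It is still the safer covariate, because it is an admission variable, whereas the diagnosis of infarction may be made after randomisation.

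**A stronger reading.** A reader might infer that infarct status swamps any drug effect on the enzymes, or that the comparison is biased. The documents do not support this. The error rate holds, they give no enzyme figures, and large effects often remain detectable under the assumed inputs: for a 50 % reduction with the second set of assumptions and a fivefold ratio, unadjusted power is 84 % against 97 % adjusted.

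**Conclusion.** The point holds as one of precision. The main comparison of CK-MB and troponin T AUC is valid, but it leaves out a strong candidate covariate that is already collected, and allocation does not balance that factor. Under the first set of assumptions the loss corresponds to 15-107 % more patients, provided the drug effect is common to all patients. If the effect is confined to infarction patients, the gain from adjusting the pooled test is small. The documents cannot place the trial within these ranges. Since this is one of several secondary endpoints in a pilot, the change is desirable but not essential.

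**What to change.** Before unblinding, state that log CK-MB AUC and log troponin T AUC will each be analysed with a linear model containing treatment and ST-elevation infarction at admission, with the treatment effect given as a ratio and its 95 % confidence interval. The unadjusted *t* test can be kept as a supporting result.

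The cost is one sentence and one degree of freedom per model, with no new data. The diagnosed-AMI subgroup analysis can stay as planned.

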### Sample size estimation

The primary outcome is feasibility and the area under the NSE curve (NSE AUC) at 72 hours. Since no difference in feasibility is expected and the trial is designed as a pilot study, we have chosen to power this study according to differences in the NSE AUC. A difference of 20 % is defined as the minimal clinically relevant difference. Previous studies have found a value of approximately 20 μg/ml (25–75 % CI 10–45) at 72 hours [21]. We expect a mean AUC at 72 hours of 50 μg/ml*day, assuming an SD of 30 % of the mean AUC. The α is set at 0.025 (co-primary endpoint), which gives a power of 90 % if 50 patients are included in both groups. A 10 % loss of final measurement is expected (patients expiring before full 72 hours). Therefore, we aim to include 120 patients in total.

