### Statistical analysis plan

#### General principles

The general principles for statistical analyses will be:Analyses will be performed according to the intention-to-treat principle with patients lost to follow-up included in the denominator [22].A two-sided significance level of 0.025 will be applied to the primary endpoints and 0.05 will be applied to the secondary endpoints.The two trial sites will be asked to complete all CRFs and other forms if missing data is found in the electronic database. Missing data will be reported in the publication.More than 5 % missing data in outcome variables (see Endpoints) will result in multiple imputation with the creation of 10 imputed datasets to be analysed separately and then aggregated into one estimate of the intervention’s effect on the primary and secondary endpoints [23, 24].

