#### Baseline data

The predefined baseline variables will be as follows:SexAgeComorbidities (pre-morbid CPC, NYHA class 3 or worse, previous myocardial infarction, ischemic heart disease, previous arrhythmia, previous cardiac arrest, arterial hypertension, transient ischemic attack or stroke, epilepsy, diabetes, asthma or chronic obstructive pulmonary disease, chronic haemodialysis or peritoneal dialysis, hepatic cirrhosis, haematological malignancy, other malignancy, AIDS, alcoholism, intravenous drug abuse, or other immunodeficiency)Previous percutaneous coronary interventionPrevious coronary artery bypass graftPrevious valvular surgeryImplantable cardioverter-defibrillator and/or pacemakerPre-hospital variablesLocation of cardiac arrestBystander witnessed arrestBystander CPRShockable primary rhythmTime to basic life supportTime to advanced life supportTime to ROSCAdmission variablesFirst measured temperatureGlasgow Coma ScoreShock at admissionST-elevation acute myocardial infarctionpHLactateCreatinine

Possible differences in baseline characteristics between the treatment groups will be analysed and displayed in Table 1. Continuous variables will be presented as mean ± SD, and differences will be analysed with the *t* test. In case of skewed data, continuous variables will be presented as median (inter-quartile range) and a *t* test will be applied following logarithmic transformation; secondarily, a non-parametric Mann-Whitney test will be applied. Categorical variables will be presented as *n* (%) and differences will be analysed with the chi-square test.

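### The two-test rule for secondary and tertiary outcomes does not suit the ordered CPC and mRS scales at 90 and 180 days, and one permitted reading loses much of the power

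*Protocol article*

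**What the plan says.** The section on secondary and tertiary outcomes gives one rule for group comparisons: an independent-sample t test or a chi-square test ("test or chi-Square test depending on the variable being numerical or categorical"). For skewness it adds: "In case of skewed data, logarithmic transformation will be applied to approximate normal distribution". Survival is handled separately with proportional hazards models.

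The Endpoints section lists CPC and mRS at 90 days as secondary and at 180 days as tertiary. It does not say whether they are scored, categorised or dichotomised. The 30-day composite in the same list does have a cut: "defined as the modified Rankin Scale (mRS) 4–6 at 30 days (telephone assessment".

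A rank test appears only under Baseline data, for skewed baseline variables: "secondarily, a non-parametric Mann-Whitney test will be applied". No ordinal or rank method is named for any outcome.

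On significance levels, General principles states: "A two-sided significance level of 0.025 will be applied to the primary endpoints and 0.05 will be applied to the secondary endpoints".

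**The concern.** CPC and mRS are ordered categories with death at the bad end. A rule that divides variables into numerical and categorical has no natural place for them, and the two classes lead to tests that behave very differently on the same data. A chi-square test over all levels would give the same result if the categories were shuffled. A t test uses the order but treats each step, including the step to death, as equally large.

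These scales are the only functional outcomes after day 30. The Discussion acknowledges that the NSE area under the curve is a surrogate, so they are the later check on whether an NSE effect reaches patients. The Abstract gives the 180-day scales prominence by naming them among the secondary endpoints. The article also says that it aims to limit data-driven reporting, and a test that can be chosen once the data are seen works against that aim.

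**Working it through.** **The plan's own figure.** There is none on this point. The only power statement concerns the NSE area under the curve. No distribution, target effect or power is given for CPC or mRS.

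**Inputs from the article.** 120 patients allocated one-to-one, so 60 per arm. Two-sided 0.05 for secondary endpoints; no level is stated for tertiary endpoints, and 0.05 is assumed there too. In-hospital mortality of 30–50 % (Background), used to anchor the share in the death category.

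**Assumed inputs.** Control distributions, best to worst level, in per cent:
- CPC 1–5: 48/8/4/2/38, 30/20/15/5/30 and 38/6/4/2/50.
- mRS 0–6: 20/18/10/7/5/2/38, 12/14/14/12/10/8/30 and 13/13/10/6/5/3/50.

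Treatment effect: common odds ratios (OR) of 1, 1.5, 2, 2.5 and 3.

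**Step 1: apply the shift.** If c is the control proportion at or below a level, the treated proportion is OR·c/(1 − c + OR·c). Take the first mRS distribution at OR 2. The cumulative proportions 0.20, 0.38, 0.48, 0.55, 0.60 and 0.62 become 0.333, 0.551, 0.649, 0.710, 0.750 and 0.765. Death falls from 38 % to 23.5 %, and mRS 0–3 rises from 55 % to 71.0 %.

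**Step 2: check that case by formula.**
- Seven-level chi-square: the noncentrality is 60·Σ(p − q)²/(p + q) = 4.41. With 6 degrees of freedom and a critical value of 12.59, power is 29.7 %.
- t test on scores 0–6: the means are 3.17 and 2.24 and the variances 6.14 and 5.61. The standardised difference is 0.928/√((6.14 + 5.61)/60) = 2.10. Against a critical value of 1.98, power is about 54.7 %.
- Chi-square on mRS 0–3 versus 4–6: (0.1597 − 1.96·0.0882)/0.0869 = −0.15, so power is about 44 %.

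**Step 3: simulate every distribution** (20,000 trials per scenario, tie-corrected Mann-Whitney). For the case in Step 2 the simulation gives 29.7 %, 54.4 % and 44.4 %, and 55.6 % for Mann-Whitney, in agreement with the formulas. Ranges over the three distributions per scale at OR 2:

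| Test | CPC | mRS |
|---|---|---|
| Chi-square, all levels | 30–34 % | 29–30 % |
| Chi-square, dichotomised (CPC 1–2 vs 3–5; mRS 0–3 vs 4–6) | 44–48 % | 44–49 % |
| t test on scores | 48–53 % | 54–57 % |
| Mann-Whitney | 49–54 % | 55–57 % |

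Power of the all-level chi-square divided by that of Mann-Whitney:

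| OR | CPC | mRS |
|---|---|---|
| 1.5 | 0.53–0.59 | 0.47–0.49 |
| 2 | 0.61–0.62 | 0.52–0.53 |
| 2.5 | 0.70–0.73 | 0.64 |
| 3 | 0.78–0.82 | 0.75–0.76 |

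At OR 1.5 to 3 the t test keeps 0.97–1.01 of the Mann-Whitney power. The dichotomised chi-square keeps 0.85–0.99 (CPC) and 0.80–0.93 (mRS). At OR 1 the all-level chi-square rejects in 3.3–5.0 % of trials.

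**Step 4: the numerical reading.** Power is not the difficulty here. The logarithm of 0 does not exist, so the stated remedy for skewness cannot be applied to mRS as scored without an added constant, which the article does not mention. A logarithm also cannot make a score with peaks at both ends approximately normal.

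**The case against.** The strongest reply is that this is a condensed article, that the coding of secondary and tertiary scales is often left to the full plan, and that the only mRS coding given is binary, for which a chi-square test is suitable. Part of this stands. The article nowhere commits to a chi-square test over all levels, so that test is a permitted reading and not the stated plan. But the point does not rest on an omission. The article states one rule for all these outcomes under a heading that calls it the statistical analysis plan, and it sets a cut for mRS at 30 days while setting none at 90 and 180 days.

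A reader might infer that the plan as a whole ignores the ordering and halves the power. The calculation does not support that. The t test uses the order and matches the rank test. The loss reaches about half only for the all-level chi-square at modest effects: mRS at odds ratios of 1.5–2, and CPC near 1.5.

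A reader might also infer that sparse cells make the seven-level chi-square invalid. With no treatment effect it rejected no more often than the nominal 5 %, so the problem is inefficiency and not false positives.

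It is also fair to say that the simulated data follow proportional odds, which favours the ordinal methods, and that odds ratios of 2–3 are large. The exact percentages are therefore illustrative.

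**Conclusion.** The point holds in this limited form. The rule suits neither possible classification of CPC and mRS at 90 and 180 days, and it leaves the choice between them open. Treated as categorical over all levels, the comparison has about 29–34 % power against 49–57 % for a rank test at a common odds ratio of 2. Treated as numerical, the power is kept, but the estimate is hard to interpret and the log step fails at mRS 0.

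The figures rest on assumed distributions (death 30–50 %), assumed proportional odds and 60 per arm; the article supplies only the sample size, the 0.05 level for secondary endpoints and the mortality range. The endpoints are secondary or tertiary in a pilot powered on NSE alone, so the co-primary conclusions, the survival analyses and the 30-day composite are untouched. Even the better tests have only moderate power at an odds ratio of 2. The gain from a change is a fixed, interpretable analysis that does not waste information; it does not turn these into confirmatory endpoints.

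**What to change.** In the section on secondary and tertiary outcomes, state that CPC and mRS at 90 and 180 days will each be compared with one prespecified ordinal analysis: a proportional-odds model with death as the worst category, reporting the common odds ratio with its 95 % confidence interval. Name Mann-Whitney as the assumption-light check and keep the mRS 4–6 split as supportive. Restrict the t test and its log transformation to outcomes that are truly continuous. The 30-day composite can stay as it is.

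This costs a few sentences and no new data, and should be settled before unblinding. The one small drawback is that the common odds ratio relies on approximate proportionality, which is why the rank test is kept beside it.
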